### Primary Outcome: Hemoglobin A_1c_

Participants will self-report their HbA_1c_ levels, a measure of the average blood glucose levels over the past 3 months, 5 times throughout the study: at baseline, week 12 (3 weeks postintervention), week 24 (3 weeks after the 3-month postintervention assessment), week 36 (3 weeks after the 6-month postintervention assessment), and week 57 (at the 12-month postintervention assessment). At each assessment, participants will also report the date when they received this HbA_1c_ reading to verify that it falls in the correct time frame.

### Secondary Outcomes

#### Diabetes Distress Scale

Diabetes distress scale [68] is a 17-item scale that assesses the extent to which certain diabetes-related situations have been a problem for participants. Each item represents a potential problem area for individuals living with diabetes (eg, feeling that I am often failing with my diabetes routine), and participants indicate the extent to which they have been distressed or bothered by that issue during the past month on a scale ranging from 1 (*not a problem*) to 6 (*a very serious problem*). The responses are averaged so that scores can range from 1 to 6, where higher scores indicate higher levels of distress, and scores of 3 or greater are considered to be clinically significant levels of diabetes-related distress.

#### Measures of Medication Adherence Scale

Measures of Medication Adherence Scale [69] is a 4-item self-report measure of medication adherence and thus will only be shown to participants who indicate they are currently prescribed medication for diabetes on a preceding question. This scale will be modified slightly to ask participants specifically about adherence to diabetes medication over the past week. For each item (eg, Over the past week, did you ever forget to take your diabetes medicine?), participants indicate *yes* or *no*. All *yes* responses are coded as 0, and *no* responses are coded as *1*. The responses are then summed so that higher scores indicate greater medication nonadherence.

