Observational studies of Happify Health users demonstrate that usage over 8 weeks is associated with more than a 27% increase in positive emotions, and high-use participants see even greater improvement [57,58]. A later RCT also demonstrated that Happify Health users who completed at least two activities per week reported significantly more improvement in depression, anxiety, and resilience than those who completed fewer activities or participants assigned to the control group [59]. Similar effects were obtained from RCTs focused specifically on people with higher levels of emotional or workplace distress [60]. More recent research also suggests that Happify Health use improves subjective well-being among people living with chronic physical conditions, including, but not limited to, diabetes, at the same rate as those without chronic conditions [61]. Consequently, there is preliminary evidence to suggest that Happify Health could effectively improve subjective and psychological well-being among individuals diagnosed with type 2 diabetes. However, no research has examined whether Happify Health use could also positively improve outcomes associated with their diabetes, including how well they manage their condition, their level of diabetes-related distress, and physical outcomes such as HbA_1c_ levels.

Therefore, in this study, our goal is to examine whether Happify Health use over the course of 8 weeks also helps to improve diabetes-specific outcomes. To do so, we plan to compare changes in HbA_1c_ levels among adults with poorly managed type 2 diabetes and elevated depressive symptoms who have completed 8 weeks of activities on Happify Health or 8 weeks of a sham digital intervention. Secondary outcomes include depression, positive affect, and other diabetes-specific outcomes such as medication adherence, diabetes-related distress, and diabetes-related self-care activities. In addition, although many other studies (particularly mindfulness and PP interventions) did not examine long-term effects, we plan to explore the long-term effects of Happify Health use on both primary and secondary outcomes at 3, 6, and 12 months postintervention.

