### Analysis Plan

We plan to analyze the changes in primary and secondary outcomes across the 2 conditions using hierarchical linear modeling (HLM). We will compute the change trajectories on each outcome over the course of the study assessments (ie, at baseline, immediately postintervention, and at 3-, 6-, and 12-month follow-ups). These trajectories will then be averaged together within each condition, so we can compare the trajectories for each outcome across the 2 conditions to determine if there was greater improvement in the positive emotion regulation skills intervention group relative to the control group.

We plan to use participants’ daily assessments in 2 ways. First, we will compute growth trajectories for each participant using their daily assessments to explore when people tend to experience improvements in diabetes-related distress, diabetes regimen adherence, and mood during the intervention. Second, as retrospective reports can sometimes lead to inflated or inaccurate information compared with daily assessments [75], we will use daily assessments to compute weekly averages for diabetes-related distress, diabetes regimen adherence, and mood during and after the intervention. These weekly averages will then be used as outcome variables in the same HLM analyses described earlier.

Previous research on the impact of health care interventions on people with poorly managed diabetes suggests that effects may be most effective among people with especially poor glycemic control or HbA_1c_ levels above 9.5% [76]. Consequently, we plan to examine the effects of baseline HbA_1c_ as a moderator of the effects of the intervention on changes in the primary and secondary outcomes. Similarly, we also plan to examine the effects of baseline depressive symptoms as a moderator of the effects of the intervention. Finally, given that the effects of Happify Health use are typically moderated by usage [57-61], we plan to examine the effects of frequency of usage as another moderator of changes in the primary and secondary outcomes.

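### The stated coding and the stated direction of the medication adherence score contradict each other

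*Protocol article*

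**What the plan says.** The relevant text is in the protocol article, Methods, Secondary Outcomes, under Measures of Medication Adherence Scale. The scale "is a 4-item self-report measure of medication adherence", shown only to participants who are prescribed diabetes medication. The one example item reads "Over the past week, did you ever forget to take your diabetes medicine", answered yes or no. The coding rule is "All *yes* responses are coded as 0, and *no* responses are coded as *1". The next sentence gives the scoring and its direction: "The responses are then summed so that higher scores indicate greater medication nonadherence".

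Medication adherence is a named secondary outcome. Objectives of This Study lists "other diabetes-specific outcomes such as medication adherence, diabetes-related distress, and diabetes-related self-care activities" among the secondary outcomes, and Table 1 schedules the scale at baseline, week 10 and the 3-, 6- and 12-month follow-ups. The Analysis Plan compares trajectories on each outcome between the arms "to determine if there was greater improvement in the positive emotion regulation skills intervention group relative to the control group".

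**The concern.** Three adjacent statements do not fit together: an item that asks about a lapse, a coding rule that gives the lapse answer the lower value, and a label that says the higher total is the worse one. With lapse items, any two of these exclude the third.

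The planned comparison is about improvement, so someone must decide whether a rising or a falling score counts as improvement. An analyst who codes the data by the first sentence and reads the result by the second would call a benefit a harm, and a harm a benefit. The same would apply to the moderator analyses by baseline HbA1c, baseline depressive symptoms and usage, which the Analysis Plan extends to the secondary outcomes.

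Two features of the plan make the written rule matter. The Results section gives data storage and protocol implementation to one group and all data analyses to another, so the analysts may rely on the article's text. It also allows postintervention results to be presented or published while follow-up continues. In addition, the daily regimen item records medication taken as prescribed as a favourable response, so a misread scale would appear to disagree with the daily data.

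**Working it through.** **Inputs, all from the Measures of Medication Adherence Scale paragraph:** four items; yes = 0 and no = 1 for all items; score = sum of the items, range 0 to 4; in the example item, yes means a lapse.

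**Step 1. Score by number of lapses, if all four items are lapse items.** With L lapses there are 4 − L no answers, so the documented score is S = 0 × L + 1 × (4 − L) = 4 − L.

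| Lapses (L) | Documented coding (yes = 0, no = 1) | Reversed coding (yes = 1, no = 0) |
|---|---|---|
| 0 | 4 | 0 |
| 1 | 3 | 1 |
| 2 | 2 | 2 |
| 3 | 1 | 3 |
| 4 | 0 | 4 |

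Enumerating all 16 answer patterns gives the same mapping. Under the documented coding the score falls as lapses rise, so the stated direction is not reproduced. Under the reversed coding it is.

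**Step 2. Could the three items not shown rescue the label?** Suppose k of the four items are worded so that yes means adherent, with yes still coded 0 for all of them. A fully adherent participant then scores 4 − k and a fully nonadherent one scores k.

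| k | Fully adherent | Fully nonadherent |
|---|---|---|
| 0 | 4 | 0 |
| 1 | 3 | 1 |
| 2 | 2 | 2 |
| 3 | 1 | 3 |
| 4 | 0 | 4 |

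The label needs k > 4 − k, that is, at least three of the four items. The displayed item is not worded that way, so k = 4 is excluded and only k = 3 would remain. At k = 3 the sum would still mix items that point in opposite directions.

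**Step 3. Consequence if both sentences are applied.** The article gives no expected values, so the following rates are assumed for illustration only: probability of a yes per item 0.40 under sham and 0.30 under intervention, meaning that the intervention arm adheres better.

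- Documented coding: 4 × (1 − 0.30) − 4 × (1 − 0.40) = 2.80 − 2.40 = +0.40. Read with the stated label, this is 0.40 points more nonadherence in the arm that adheres better.
- Reversed coding: 4 × 0.30 − 4 × 0.40 = 1.20 − 1.60 = −0.40. Read with the same label, this is correctly less nonadherence.

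One score is 4 minus the other. Reversing the coding therefore changes the sign of every difference and slope, and leaves the absolute size, the standard error and a two-sided p-value as they were.

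**The case against.** The strongest reply is that this is probably a slip in one sentence, with no effect on the analysis. If the last sentence should say adherence, the coding is right and nothing is misreported. If the coding sentence is the slip, the data would be scored in the labelled direction, and again nothing is misreported. The first possibility has some support: the article calls the scale a measure of adherence and names the outcome medication adherence, which fits the coding. This much stands. A reader might infer that any effect on this outcome will be reported with the wrong sign, but the article supports that only if both conflicting sentences are applied.

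A reader might also infer that the error reaches the primary result, because adherence lies between mood and HbA1c. The article does not support this. Diabetes and Mental Health links depression to poorer medication compliance and from there to preventable hospitalizations and costs; the path it draws explicitly from depression to HbA1c runs through diabetes-related distress. The Analysis Plan lists moderators and no mediation analysis using this score. The rule for discontinuing the study after the preliminary analysis refers to primary outcomes only.

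It is also fair to say that only one of the four items is shown. That limits certainty, but Step 2 shows how far the unseen items would have to differ from the one displayed.

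Finally, the answers are collected as yes or no, so the score can be re-derived at any time before reporting. This argues against treating the point as critical. It does not remove the contradiction, which lies in two complete sentences that the article chose to specify and is not a detail left to another document.

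**Conclusion.** The contradiction is real and can be verified from one paragraph. As written, the coding makes higher scores mean better adherence, with 4 for no lapses and 0 for four lapses, while the label says the reverse. No other section restates or corrects the direction.

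The consequence is conditional. If both sentences are followed, the direction of interpretation on this one secondary outcome is fully reversed. The magnitude of the effect, its two-sided p-value and the primary HbA1c analysis are unaffected.

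The conclusion assumes that the three items not shown are worded as lapses like the displayed one, or at least that they are not all worded the opposite way. The statement about the p-value assumes two-sided testing, as the article gives no sidedness. Which of the two sentences is the error cannot be settled from the article. The point should be fixed before analysis, but it does not threaten the trial's main conclusion.

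**What to change.** Choose one of two consistent versions and state it in the protocol:

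- keep yes = 0 and no = 1, and say that higher totals mean greater medication adherence; or
- code yes = 1 and no = 0, and keep the statement that higher totals mean greater nonadherence.

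Then confirm that all four items are worded in the same direction; if any is not, reverse-code it explicitly. Check that the scoring code, and the direction counted as improvement in the hierarchical linear model and its moderator analyses, match the chosen version before any analysis of this outcome.

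The cost is one line of text and a check of the scoring code. Design, data collection and sample size do not change, and answers already collected can be rescored.

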#### Summary of Diabetes Self-Care Activities

Summary of diabetes self-care activities [70] is an 11-item measure of self-reported adherence to diabetes self-care activities. For 10 items, participants indicate on how many days they engaged in self-care activities related to diet (eg, How many of the last 7 days have you followed a healthful eating plan?), exercise (eg, On how many of the last 7 days did you participate in at least 30 min of physical activity?), blood sugar testing (eg, On how many of the last 7 days did you test your blood sugar?), and foot care (eg, On how many of the last 7 days did you check your feet?) over the past week on a scale ranging from 0 to 7. One item also asks participants to indicate the frequency of smoking over the past week (ie, Have you smoked a cigarette, even 1 puff, during the past 7 days?) on a scale ranging from 0 (*no*) to 1 (*yes*); participants who respond yes are then asked to indicate how many cigarettes they smoked on an average day. Separate scores are then created for each subscale.

#### Patient Health Questionnaire

PHQ-9 [62] is a 9-item scale measuring depressive symptomology. Each item represents a depressive symptom (eg, feeling down, depressed, or hopeless), and participants indicate how often they have been bothered by each symptom over the past 2 weeks on a scale ranging from 0 (*not at all*) to 3 (*nearly every day*). The responses are then summed such that scores can range from 0 to 27, and higher scores indicate more severe depressive symptoms.

#### Patient-Reported Outcomes Measurement Information Systems: Positive Affect Subscale

Participants will also complete the positive affect subscale of the Patient-Reported Outcomes Measurement Information Systems [71] scale. This subscale asks participants to indicate how much they felt each of the 15 emotions (eg, “I felt cheerful”) over the past 7 days on a scale ranging from 1 (*not at all*) to 5 (*very much*). Items are summed so that higher scores indicate greater positive affect.

### Daily Assessments

#### Diabetes-Related Distress

We will assess daily levels of diabetes-related distress with a single item (ie, How would you rate your diabetes-related distress, on average, over the past 24 hours?) rated on a scale ranging from 1 (*very low*) to 7 (*very high*).

#### Diabetes Regimen Adherence

We will assess participants’ daily regimen adherence using a single item (ie, Which of the following activities in your diabetes regimen did you complete over the past 24 hours?) where participants check any of the following options that apply to their situation: monitored blood sugar, ate according to healthy eating diet, engaged in physical activity, took diabetes medication as prescribed, or did not follow my diabetes regimen at all.

#### Daily Mood

We will assess participants’ daily mood with a single item (ie, “How depressed did you feel, on average, over the past 24 hours?”) rated on a scale ranging from 1 (*not at all*) to 7 (*extremely*) [72].

### Procedures

Participation in this study will take place over approximately 14 months, including an 8-week intervention (or corresponding control) delivered via Happify Health as well as follow-up assessments at 3, 6, and 12 months postintervention. To ensure that HbA_1c_ levels reported postintervention reflect average glucose levels only after starting the intervention, all participants will begin the study within 3 weeks of obtaining their most recent HbA_1c_ levels. Participants who indicate that their most recent HbA_1c_ levels were obtained before that when contacted by phone will wait to begin the study until they obtain their following HbA_1c_ measurement and researchers confirm that they meet the inclusion criterion.

Once participants are ready to begin the study, they will be directed to complete 1 week of daily assessments without exposure to either condition. Participants who complete fewer than 5 of these assessments will be disqualified from the study. Those who complete at least five of the daily assessments during this qualifying period will be directed to download the mobile app and complete the regular onboarding questionnaire for Happify Health; participants will be randomly assigned to either the positive emotion regulation skills intervention group or the control group upon completing these questions. Following randomization, participants will be prompted to complete the baseline assessment.

Participants will then be instructed to begin using their assigned version of Happify Health. Although participants will not be given explicit instructions on how often they should use the platform, they will be encouraged to engage with the platform daily. Participants will receive daily push notifications on their mobile device to remind them to access the platform and answer daily questionnaires, and they will also receive weekly emails as part of the Happify Health platform to help keep them engaged with the program. In addition, to improve use rates and participant retention, research staff will call participants to inquire about problems when a participant has not engaged with the Happify Health platform at all for 1 week.

After 8 weeks, participants will be instructed to complete the postintervention assessment; this assessment will be identical to the baseline with the exception of HbA_1c_ assessment, which will occur 3 weeks later via the Happify Health app. After completing this assessment, participants will receive an email instructing them to answer daily questions for 1 week and to remind them that we will contact them again in 3, 6, and 12 months for follow-up assessments and that they should continue to use their assigned version of Happify Health as they see fit. Participants will then receive emails instructing them to complete each of the 3-, 6-, and 12-month assessments, which will also be accompanied by 1 week of daily assessments at each follow-up period. Table 1 provides the schedule of activities. To improve participant retention, participants who do not complete the postintervention, 3-, 6-, and 12-month assessments will also receive a reminder phone call from the research staff.

**Table 1 table1:** Schedule of activities for prescreen, intervention period, and follow-up assessments.

Assessments		Time										
		Prescreen	Week 1: qualifying period	Week 2: baseline and first week of intervention	Weeks 3-9: intervention	Week 10	Week 12	Week 21: 3-month follow-up	Week 24	Week 33: 6-month follow-up	Week 36	Week 57: 12-month follow-up

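### The 3-week start rule cannot keep pre-intervention glucose out of the week-12 HbA1c, which still covers about 1 to 3 weeks before the intervention began

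*Protocol article*

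**What the plan says.** The Protocol article, under Procedures, states an aim and a rule meant to secure it.

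- Aim: "To ensure that HbA_1c_ levels reported postintervention reflect average glucose levels only after starting the intervention".
- Rule: "all participants will begin the study within 3 weeks of obtaining their most recent HbA_1c_ levels". People whose last reading is older wait for their next one.

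The other relevant statements are these.

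- Under Primary Outcome, HbA1c is described as "a measure of the average blood glucose levels over the past 3 months".
- Under Procedures, participants first "complete 1 week of daily assessments without exposure to either condition".
- Table 1 then has "Week 2: baseline and first week of intervention", followed by "Weeks 3-9: intervention".
- The first follow-up HbA1c is at "week 12 (3 weeks postintervention" under Primary Outcome. Procedures agrees: the 8-week assessment omits HbA1c, "which will occur 3 weeks later via the Happify Health app".
- Later readings are at weeks 24, 36 and 57. Participants also report the date of each reading, so that its timing can be checked.

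**The concern.** The rule limits how old the baseline reading may be. The aim concerns a different reading, the one taken after the intervention. Whether that reading is free of pre-intervention glucose depends on the time from first use to the follow-up draw, and the rule sets no minimum for that interval.

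HbA1c is the primary outcome and week 12 is its first value after baseline. The Results section plans to analyse, and possibly present or publish, postintervention results while follow-up continues. It also plans an early look, with possible discontinuation, once 20% of the target sample has finished the 8 weeks. If the week-12 value is used in either place, readers would take it as fully postintervention when part of it is not. Any real effect would then look smaller than it is.

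**Working it through.** **Inputs** (Primary Outcome, Procedures, Table 1): run-in 1 week, intervention 8 weeks, HbA1c lag 3 weeks, averaging window 3 months.

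**Step 1. Reproduce the schedule.** 1 + 8 + 3 = 12, so the reading falls in study week 12, as stated. The later readings also fit: 21 + 3 = 24 and 33 + 3 = 36.

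**Step 2. Time from intervention start to the reading.** The intervention starts when week 1 ends. A draw at the start of week 12 comes 11 − 1 = 10 weeks later; one at the end of week 12 comes 12 − 1 = 11 weeks later. First use later in week 2 would shorten this.

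**Step 3. Window length.** The article says 3 months. That is about 13 calendar weeks, but Table 1 spaces its 3-month and 6-month visits 12 weeks apart (week 21 to week 33), so both are used.

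**Step 4. Overlap.** Pre-intervention weeks = window − weeks since start. Share before start = pre-intervention weeks / window. Share kept = weeks since start / window; this takes every week as equally weighted and the effect as constant from the first day.

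| Window | Draw in week 12 | Weeks before start | Share before start | Share of effect kept |
|---|---|---|---|---|
| 13 weeks | end | 13 − 11 = 2 | 2/13 = 15% | 11/13 = 85% |
| 13 weeks | start | 13 − 10 = 3 | 3/13 = 23% | 10/13 = 77% |
| 12 weeks | end | 12 − 11 = 1 | 1/12 = 8% | 11/12 = 92% |
| 12 weeks | start | 12 − 10 = 2 | 2/12 = 17% | 10/12 = 83% |

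No case gives zero.

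**Step 5. Can the rule remove the overlap through routine testing?** Suppose the next test falls exactly one window (W weeks) after a baseline drawn b weeks before study start, with b from 0 to 3. Counting the run-in as part of the study, as Procedures does, the time since intervention start is W − b − 1. The overlap is then b + 1, or 1-4 weeks. Recruitment Strategy can be read as placing study start after the run-in. The overlap is then b, and it is zero only if the baseline is drawn on the day of first use and the retest waits a full 3 months, which is past week 12.

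**Step 6. When is a reading clear?** At run-in + window: the end of week 1 + 12 = 13, or 1 + 13 = 14. For weeks 24, 36 and 57, even the 13-week window opens no earlier than the end of weeks 11, 23 and 44. All are after intervention start.

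**Step 7. Illustration of the cost.** The article gives no effect size or standard deviation, so the effects here are assumed. For a simple two-group comparison at week 12 with 200 per arm (Participants section), two-sided 5% and no dropout, power is approximately Φ(d × f × √(200/2) − 1.96), where d is the standardized effect and f the share kept (10/13 to 11/12).

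- d = 0.2: 52% undiluted, 34-45% diluted.
- d = 0.3: 85% undiluted, 64-79% diluted.
- d = 0.4: 98% undiluted, 87-96% diluted.

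This is not the power of the planned model, which uses all the readings.

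**The case against.** **The rule is not idle.** If people are tested about every 3 months, starting soon after one test pushes the next one later relative to first use. That stands: the rule can reduce the overlap. Step 5 shows that it cannot remove it by week 12.

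**Reading dates are checked.** They are, and the exact acceptance window may well be in the full protocol. But a reading dated correctly in week 12 is still too early, so the check cannot supply the missing weeks.

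**Week 12 is not singled out as the primary result.** Correct. The Analysis Plan compares trajectories over all assessments, and three of the four follow-up readings are unaffected. The early look is triggered by completing 8 weeks, before a participant's week-12 HbA1c is due, so the consequence there is conditional on that value being used.

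**A reader might infer that week 12 shows only about half the effect.** That needs an assumed gradual build-up, and the article gives no effect shape. Build-up also happens after the start, so it does not contradict the stated aim. If an effect rose linearly over 56 days and then held, a reading 91 days after start, with no pre-intervention time in it, would still show only (28 + 35)/91 = 69%.

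**A reader might also infer that week 24 should become the main contrast.** Its window opens at the end of week 11 or 12, after the intervention ends in week 9, and contains none of the 8 treated weeks. It measures persistence, whereas the trial states both short- and long-term aims.

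**Conclusion.** The concern holds for the week-12 reading. The article claims a property of its primary outcome that its own schedule and its own definition of HbA1c rule out: 10-11 weeks is less than 3 months.

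The overlap is 2-3 weeks (15-23%) with a 13-week window and 1-2 weeks (8-17%) with a 12-week window. The share of a real effect still visible, about 77-92%, also rests on equal weighting and an effect that is constant from the start. The existence of the overlap rests on neither assumption.

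Both arms share the same window, so the consequence is dilution toward zero if there is a real effect, and no added false-positive risk. The trial is not invalidated, but the claim should be corrected before week-12 results are analysed or shared.

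**What to change.** Remove or correct the claim that the 3-week rule leaves only glucose from after the intervention began, and reconcile the stated aim with the week-12 timing. Then choose one of two courses.

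1. Set the first follow-up draw at 3 months or more after first intervention use, about the end of study week 13 (12-week window) or 14 (13-week window), judged by the reported reading date.
2. Keep week 12, and analyse and report it as an early, partly exposed reading. Carry that label into the early postintervention report and into any early look that uses the value.

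Under either course, describe the 3-week rule as what it is: a limit on the age of the baseline that may also delay the next routine test.

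The cost is small. The first course brings the first HbA1c result 1-3 weeks later. The second changes no dates but describes the first result less favourably.
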